## Abstract

Worldwide, 3.8 million out-of-hospital cardiac arrests (OHCA) occur annually. RescQ™ is a 12-month, non-randomised, prospective feasibility pilot evaluating a structured support pathway for adult bystanders involved in out-of-hospital cardiac arrest of presumed medical or cardiac aetiology across Essex, United Kingdom.

The pathway was developed to address the absence of a nationally standardised post-event support process for bystanders who witness, call emergency services, or assist with resuscitation. Attending ambulance clinicians offer brief on-scene signposting and register consenting adult bystanders through a dedicated digital application.

Registration triggers a single text message or email linking to the RescQ™ website, which provides information on common physical and psychological reactions after involvement in cardiac arrest, coping strategies, lived-experience videos and sources of further support. Bystanders can self-refer to a liaison officer for structured supportive contact, psychological screening (using Clinical Outcomes in Routine Evaluation and the National Stressful Events Survey Short Scale), event-related discussion, signposting and onward referral where required.

The primary outcome is feasibility, assessed through ambulance clinician uptake, bystander website access and acceptability to ambulance clinicians and bystanders. Secondary outcomes include digital engagement, psychological screening data, liaison officer activity, onward referral, satisfaction and service-delivery resource use.

The project was reviewed by the West of Scotland Regional Ethics Committee and classified as a service evaluation. At the time of revised submission, the 12-month pilot has been completed, and data analysis is underway.

## Introduction

Worldwide, there are 3.8 million out-of-hospital cardiac arrests (OHCA) recorded annually^1^ of which 115,000 are reported to the ambulance services in the UK and resuscitation is attempted in around 43,000.^2^ More than half of these events are witnessed and around 70% occur at home^2^, ^3^, ^4^ Bystanders to these events may be family members, friends, colleagues, or total strangers, with rate of bystander cardiopulmonary resuscitation (CPR) varying substantially between regions, from 13% to 82%.^5^ In England, national OHCA registry data reported bystander CPR in 72.6% of cases.^2^

The experience of witnessing, providing first aid or helping in an OHCA can be extremely distressing and may have lasting emotional and psychological consequences for those involved.^6^, ^7^, ^8^, ^9^ Bystanders who perform CPR or assist during an OHCA are thrust into an emotionally traumatic situation without warning, potentially leading to acute stress reactions, including hyper-alertness, intrusive memories, flashbacks, sleep disturbances, anxiety, guilt, and helplessness.^9^, ^10^, ^11^, ^12^ These emotional responses can persist for days to months, impacting the mental well-being of the bystander.^10^ Some are so traumatised that they are unable to carry on with normal day-to-day activities.^10^, ^11^, ^12^, ^13^

Post-traumatic stress symptoms (PTSS) are also common.^12^ Long-term effects such as anxiety, grief, and isolation can persist for years, with approximately 19% to 30% of bystanders experiencing high levels of distress even two years after the incident.^14^

In the time-pressured environment of an OHCA, the well-being of the bystander frequently becomes secondary, if a consideration at all.^11^, ^13^, ^15^ Family members present at the event, increasingly termed 'co-survivors' or 'key supporters', may receive some support from prehospital and hospital staff following patient admission.^16^, ^17^ However, if the patient dies at the scene, this hospital-based support is no longer available.^9^, ^11^, ^15^ Moreover, bystanders who are strangers to the patient typically do not receive any support, leaving them to cope with the emotional aftermath on their own.^18^

There is currently no standardised psychological support programme for OHCA bystanders in the UK. While some air ambulance charities and ambulance services offer aftercare following OHCA or other critical incidents, provision is inconsistent and there is no nationally standardised approach. A Norwegian study of first aid providers reported that, among those followed up beyond one month, 81% continued to report at least one symptom or functional impairment, and 19% met criteria for post-traumatic stress disorder or complex post-traumatic stress disorder.^19^

An exploratory survey at Essex Cardiothoracic Centre (ECTC) and among Sudden Cardiac Arrest UK (SCAUK) group members, assessed the psychological impact of witnessing or assisting in OHCA. Among 204 respondents, post-traumatic symptoms were prevalent across all groups, affecting 90% of untrained bystanders, 67% with prior CPR training, and 46% with advanced CPR training. Despite 74% expressing a strong need for immediate support, most received little or no formal debriefing. Advanced-trained individuals reported a more positive experience, possibly reflecting their higher rate of informal debriefing (22%).^6^

A recent scoping review identified emerging support interventions for OHCA bystanders, but found that existing provision was inconsistent, variably promoted and largely unevaluated. Few studies reported participant outcomes, and none evaluated intervention effectiveness.^20^

The RescQ™ pilot was conceived to address this critical gap. It aims to provide timely and practical psychological support for bystanders and lay-rescuers through an integrated digital platform and personalised follow-up. By embedding RescQ™ into prehospital care, the project seeks not only to support bystanders in the immediate aftermath of OHCA but also to generate evidence on feasibility, acceptability, and impact.

This manuscript describes the design and methodology of the RescQ™ feasibility pilot.

## Methods and analysis

### Design

RescQ™ pilot is a 12-month, non-randomised, prospective, observational study to support consecutive bystanders involved in OHCA of presumed cardiac/medical aetiology across Essex. This is a feasibility pilot integrating prehospital and hospital services, and patient focus groups.

### Ethics

The study was reviewed by the West of Scotland Regional Ethics Committee (REC Ref: 24/WS/0088; IRAS ID: 340729) and classified as a service evaluation, meaning formal National Health Service (NHS) REC and Health Research Authority (HRA) approval is not required. It is conducted in compliance with NHS research governance principles and General Data Protection Regulation (GDPR), with information governance and data protection frameworks established in collaboration with prehospital and hospital information teams.

### Eligibility (Table 1)

All adults (age ≥18 years), consenting bystanders who have witnessed and/or called 999 and/or directly assisted in resuscitation efforts at an OHCA of cardiac/medical aetiology. The bystanders should be willing to engage with the digital platform and/or follow-up surveys if needed.

**Table 1 t0005:** Eligibility criteria for RescQ™ (OHCA: out-of-hospital cardiac arrest; CPR: cardiopulmonary resuscitation).

**Inclusion criteria**
Consenting bystanders
Witnessed the OHCA, and/or called 999, and/or performed CPR, and/or assisted in resuscitation efforts
OHCA of presumed cardiac or medical aetiology
Willing to engage with the digital platform and/or follow-up surveys

Bystanders who cannot consent to participation or those involved in OHCA of non-cardiac/non-medical aetiology (traumatic, road traffic accidents, drug overdose, suicide, drowning) will be excluded.

### Rationale for eligibility

Bystanders who witness or assist during an OHCA are at high risk of psychological distress and are therefore the appropriate target population. Inclusion is restricted to adults (≥18 years) as the RescQ™ team works exclusively within adult services and lacks the expertise and safeguarding structures required to support a paediatric population, though bystanders under 18 are recorded for descriptive purposes.

The study is limited to cardiac/medical OHCAs, as traumatic or non-cardiac arrests involve different contexts, clinical management, and potentially more complex psychological sequelae, which fall outside the project team's expertise.

Bystanders unable to provide informed consent are excluded, as participation involves survey completion and potential LO engagement.

These criteria ensure the feasibility pilot targets those most likely to benefit, within the scope and resources of the participating teams.

### Stakeholder engagement and patient and public involvement

RescQ™ has been co-designed with input from cardiac arrest survivors, bystanders, psychologists, mental health counsellors, prehospital clinicians, and patient focus groups, who informed the website content, app design, and overall pathway structure.

The prehospital team includes representatives from the East of England Ambulance NHS Trust (EEAST), East and Herts Air Ambulance Trust (EHAAT), and East Anglia Air Ambulance (EAAA). The hospital team, based at ECTC comprises cardiologists, psychologists, occupational therapists, and mental health counsellors. The digital platform was developed in partnership with Blum Health Ltd.

Patient and public involvement is provided through the Sudden Cardiac Arrest UK (SCAUK) group, whose members contributed lived experience as survivors, co-survivors and bystanders. Contributors informed the design of the RescQ pathway, website content, tone of communication, acceptability of on-scene registration, and the need for flexible access to support.

### Geographical setting

In the UK, an OHCA typically begins when a bystander witnesses a collapse and calls 999. Call handlers guide CPR until professional help arrives. The study is being conducted in Essex (population 2.8 million), UK, within the regional OHCA response pathway served by EEAST land ambulance, and EHAAT and EAAA air ambulance services. Usually community first responders (CFRs) are often first on scene, followed by EEAST land ambulance clinician crews providing advanced life support, with air ambulance support from EHAAT or EAAA where needed.

If return of spontaneous circulation (ROSC) is achieved, patients are transferred to a local emergency department or the ECTC depending on clinical need. Family members may accompany the patient in the land ambulance or make their own way to hospital. In cases where resuscitation is unsuccessful, the patient’s body is taken to the local morgue.

While ambulance crews may offer a short debrief or leave a contact card, this is inconsistent and dependent on scene dynamics and crew workload. As a result, the psychological impact on bystanders is rarely addressed in a structured way, and those experiencing post-event distress are currently directed to primary care, with no dedicated follow-up pathway.

### Intervention (Fig. 1, Fig. 2)

#### Ambulance clinician registration

At the OHCA scene, attending ambulance clinicians provide a brief standardised debrief towards the end of resuscitation, thanking bystanders for their actions, acknowledging potential psychological impact, and offering support through the RescQ™ pilot.

Registration is completed via the RescQ™ app on EEAST iPad devices, which records the event with geo-location and timestamping and generates a unique quick response (QR) code. This can be scanned by other clinicians to register multiple bystanders, or by bystanders themselves to enter their own contact details (email or mobile number). The app also captures whether the bystander is known to the patient and records the number of bystanders under 18 or who decline registration.

Following registration, the bystander’s contact information is transferred immediately to a secure central server and automatically deleted from the ambulance clinician-facing application. Clinicians are therefore unable to access email addresses or mobile telephone numbers after the event has been registered. No additional personal information is stored within the application.

#### Digital prompt

Upon registration, bystanders receive a single text or email containing a brief introduction to the RescQ™ pilot and a secure link to the dedicated website, accessible at any time. No reminders or further unsolicited communications will be sent to respect privacy and avoid intrusion.

#### Website resources

The RescQ™ website is accessible only to registered bystanders and provides resources on the expected psychological and physical reactions to witnessing an OHCA or performing CPR, including practical advice, coping strategies, and guidance on seeking further help. Content includes psychologist-authored articles and selected open-access resources from SCAUK and the Resuscitation Council UK (RCUK).

The website also hosts 16 short videos featuring survivors, bystanders, cardiologists, psychologists, occupational therapists, and mental health counsellors, drawing on both lived experience and clinical expertise.

Bystanders requiring additional support can self-refer via a dedicated button, providing contact details and consent for follow-up from a liaison officer (LO), who will then reach out to offer further assessment and signposting.

Representative screenshots of the website homepage, resource library and liaison officer self-referral page are included in Fig. 3.

**Fig. 1 f0005:**
[figure not shown]
**Schematic overview of the RescQ™ pathway for bystanders involved in out-of-hospital cardiac arrest**. Following an on scene debrief, bystanders are offered registration to RescQ™, access to digital support resources, and escalation to liaison officer support where additional needs are identified. **OHCA:** out-of-hospital cardiac arrest; **LO:** liaison officer.

**Fig. 2 f0010:**
[figure not shown]
**Flow chart of inclusion and intervention**. Flow chart showing the inclusion pathway and intervention process for bystanders involved in out-of-hospital cardiac arrest of presumed medical or cardiac aetiology. Consenting bystanders are registered by ambulance clinicians at the scene and receive an immediate SMS/email link to the RescQ™ website. Bystanders may use the website resources independently and can self-refer for liaison officer support if additional support is required. Liaison officer contact includes initial supportive debriefing, baseline assessment of acute stress and psychological impact, follow-up assessment at two weeks, and onward signposting or referral where indicated. The number of declining bystanders and bystanders aged under 18 years is also recorded. **OHCA:** out-of-hospital cardiac arrest; **SMS:** short message service; **LO:** liaison officer.

**Fig. 3 f0015:**
[figure not shown]
**Representative screenshots of the RescQ™ website**. (A) Homepage/resource hub introducing the purpose of the website and providing access to key sections. (B) Video resource library containing lived-experience and clinician-led videos addressing emotional responses, coping strategies, peer support and information about cardiac arrest. (C) Useful articles and external links section signposting bystanders to trusted cardiac arrest, cardiopulmonary resuscitation, defibrillation and support resources. (D) Self-referral form allowing bystanders to request contact from a liaison officer. The form requires the bystander to provide contact details and confirm consent to be contacted.

#### Liaison officer

Following self-referral, the LO makes an initial telephone contact to understand the bystander's needs and arranges a follow-up session, timed at least 72 h post-OHCA, in line with guidance on acute stress reactions.^21^, ^22^ Sessions are delivered by the bystander's preferred format, face-to-face, video call, or telephone, and may include a family member or friend.

At the start, bystanders complete a numerical stress rating^1^, ^2^, ^3^, ^4^, ^5^, ^6^, ^7^, ^8^, ^9^, ^10^ and validated screening tools, National Stressful Events Survey Short Scale (NSESSS)^23^ and Clinical Outcomes in Routine Evaluation-10 items (CORE-10)^24^ as baseline measures (Supplemental Appendix A). The session structure follows the Norwegian group follow-up model^19^: bystanders are invited to speak freely, with the LO providing acknowledgement, reassurance, and detailed responses to questions based solely on information shared, avoiding speculation about clinical decisions.

There is no fixed time duration for the LO session. A post-session stress rating is recorded, and bystanders are offered signposting, open follow-up, and referral to in-house psychological counselling or respective air ambulance LO services if further support is needed.

Where bystanders enquire about patient outcome, the LO responds with supportive discussion while maintaining confidentiality. Any disclosure of outcome information is managed according to local governance procedures and consent requirements.

#### Post LO intervention feedback survey

Bystanders receiving LO support will be invited to complete a structured feedback survey two weeks post-intervention, capturing website engagement patterns, psychological outcomes (NSESSS, CORE-10), and perceived usefulness of the website and LO support (rated 0–10). Free-text fields will also capture qualitative feedback and suggestions for improvement. The full bystander and ambulance clinician satisfaction surveys are provided in Supplemental Appendix B and C.

#### Consent process

The RescQ™ pathway is entirely consent driven. Ambulance clinicians provide a brief explanation of the pathway only when clinically and operationally appropriate, after patient care and scene safety have been prioritised. Bystanders may decline registration without giving a reason.

Website access is voluntary, and registered bystanders may use the resources at their own pace without engaging further.

Liaison officer support requires a separate voluntary self-referral through the website. Bystanders requesting LO contact provide consent for follow-up and may pause or stop contact at any time. They may also decline psychological screening, signposting or onward referral.

#### Ambulance clinician training

Relevant clinicians at EEAST have received structured education on the RescQ™ pathway, including training in use of the application and communication strategies for on-scene debriefing and introducing RescQ™ to bystanders.

#### Liaison officer training, supervision and role boundaries

The liaison officer role is not intended to provide formal psychotherapy or specialist mental health treatment. Within RescQ™, the liaison officer provides structured supportive contact, event-related discussion, psychological screening, reassurance, signposting and escalation where required.

The primary liaison officer is a senior cardiology trainee with clinical experience in managing critically unwell cardiac patients and communicating with patients and families after cardiac arrest. They have direct access to consultant cardiologists, a principal psychologist and mental health counselling support for advice, supervision and escalation.

Where severe distress, safeguarding concerns, risk of harm, or scores above predefined thresholds are identified, the liaison officer follows the RescQ™ escalation pathway. This may include signposting or referral to primary care, psychological services, mental health counselling, peer support or urgent crisis services, with consent where possible.

#### Data collection and follow-up (Table 2)

Baseline data will include OHCA incidents and bystanders registered. Website analytics will capture engagement metrics including page visits, time on resources, and video views. LO records will document bystander demographics, support provided, and onward referrals made.

**Table 2 t0010:** Data items collected during the study and the sources (OHCA: out-of-hospital cardiac arrest; LO: liaison officer, CORE-10: Clinical Outcomes in Routine Evaluation-10 items; NSESSS: National Stressful Events Survey Short Scale).

**Domain**	**Data item**	**Source**	**Time point**
OHCA event	Date/time, location/geolocation	RescQ™ app	At scene by ambulance clinicians
Bystander registration	Email address or cell phone number of the bystanders consenting for registration, known/unknown to patient, Number of bystanders declining registration and those under the age of 18 years	RescQ™ app	At scene by ambulance clinicians
Digital engagement	Unique users, sessions, page views, resource views, video views, time on resources	Website analytics	On accessing website
Liaison officer support	Timing of contact, mode of contact, duration, support provided, questions/concerns raised	LO record	At LO contact
Psychological measures	Self-stress score (1–10), CORE-10, NSESSS	LO assessment/follow-up survey	Baseline and two-week follow-up
Referral/signposting	Primary care, psychologist, mental health counsellor, peer support, air ambulance LO, other services	LO record	During/after LO contact
Acceptability	Website usefulness, LO usefulness, satisfaction ratings, free-text feedback	Bystander survey	Two weeks post-LO contact
Paramedic feedback	Awareness, usability, feasibility at scene, burden, acceptability, suggestions	Paramedic survey	During/after pilot
Service delivery	Staff role, registration time, LO time, admin time, supervision/training input, platform support	Study logs	Throughout pilot

Data from LO sessions and the two-week follow-up survey will undergo qualitative thematic analysis. Where stress scores exceed defined thresholds (NSESSS >14, CORE-10 >20), and with bystander consent, onward referral will be arranged to primary care, the ECTC psychologist, a mental health counsellor, or peer support networks such as SCAUK.

#### Safety monitoring and adverse event reporting

Although RescQ™ is a low-intensity supportive intervention, processes are in place to identify and respond to potential harm. Potential concerns include worsening distress, disclosure of self-harm or risk to others, safeguarding issues, complaints, inappropriate disclosure of confidential information, or need for urgent mental health or emergency support.

Any concerns identified during liaison officer contact are documented and escalated through the RescQ™ safety pathway. With consent where possible, bystanders may be signposted or referred to primary care, mental health services, crisis services or emergency services. Serious incidents or governance concerns are reported through local NHS incident reporting processes and reviewed by the RescQ™ clinical governance team.

### Outcomes

#### Primary outcome

The primary outcome is to determine the feasibility of delivering a structured bystander support programme following OHCA using the RescQ™ digital platform.

Feasibility will be assessed across three domains: (i) ambulance clinician uptake (registration of bystanders at the scene), (ii) bystander uptake (accessing RescQ™ website), and (iii) acceptability to both ambulance clinicians and bystanders.

Ambulance clinician uptake will be defined as the proportion of eligible OHCA incidents in which at least one bystander is registered via the RescQ™ app, with ≥40% considered indicative of feasibility.

Bystander uptake will be defined as the proportion of registered bystanders who access the RescQ™ website at least once, with the predefined threshold of ≥90% considered indicative of feasibility.

Acceptability will be assessed using a combination of uptake metrics, structured feedback and free-text responses. Ambulance clinician acceptability is assessed through a feedback questionnaire addressing awareness of RescQ™, ease of using the registration application, perceived suitability of introducing the pathway at scene, perceived burden on clinical workflow and suggestions for improvement (Supplemental Appendix C).

Bystander acceptability is assessed among those accessing liaison officer support using satisfaction ratings for the website and liaison officer intervention, perceived usefulness of support in coping with the event, willingness to recommend the service to others, and free-text feedback. Website access and self-referral rates are also interpreted as pragmatic indicators of acceptability and engagement.

Feasibility and acceptability outcomes will be interpreted using predefined thresholds, summarised in Fig. 4 and Table 3.

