## Discussion

RescQ™ is a structured UK initiative to provide real-time psychological support for OHCA bystanders, integrating prehospital engagement, a tailored digital platform, and professional LO follow-up to address a critical gap in the chain of survival: the wellbeing of those who step forward to assist in resuscitation.

The RescQ™ design evolved considerably from initial conception. Early plans centred on QR code wristbands distributed at scene, but collaboration with ambulance services and SCAUK highlighted limitations around inconsistent uptake and lack of ongoing support. This led to a digital-first solution embedded within ambulance clinician workflow, enabling on-scene registration, immediate access to resources, and personalised follow-up, strengthening both feasibility and scalability.

RescQ™ is fully integrated into ambulance clinician workflow, enabling immediate bystander registration at scene. Its digital-first approach allows rapid delivery of resources, avoiding delays inherent in traditional referral pathways. The self-referral mechanism to LOs ensures personalised, flexible support, allowing bystanders to engage on their own terms and timeline.

Existing international bystander support programmes typically rely on helpline self-referral or volunteer responder app registration, leaving gaps for those who do not initiate contact or are unregistered. By embedding RescQ™ directly into the prehospital process, the programme ensures all identified bystanders are offered support, regardless of prior registration or proactive engagement.

Anticipated challenges include inconsistent ambulance clinician compliance given the high-pressure nature of OHCA scenes, variable digital literacy among bystanders, and declining engagement over time. Additionally, appropriate referral thresholds must be maintained, balancing accessible LO support with timely escalation to specialist mental health services where needed.

If proven feasible, RescQ™ has potential impact beyond OHCA, including traumatic and natural disasters. At a community level, improved bystander experience may increase confidence and willingness to intervene in future arrests. At a systems level, findings could inform NHS strategies for integrating psychosocial care into emergency response, with broader national and international relevance given the widespread absence of structured rescuer follow-up.

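### The only source listed for OHCA events is the RescQ app; if the clinician-uptake denominator is taken from it, incidents where the app was never opened are lost and uptake can only be biased upward

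*Protocol article*

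**What the plan says.** **Outcome.** The Primary outcome section defines ambulance clinician uptake as the "proportion of eligible OHCA incidents in which at least one bystander is registered via the RescQ™ app". Table 3 and the Sample size and statistical analysis section grade it green at 40% or more, amber at 30–39% and red below 30%. The numerator is tied to the app. No source is given for the denominator.

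**Sources.** Table 2 is captioned as "Data items collected during the study and the sources". Its OHCA event row reads "Date/time, location/geolocation RescQ™ app At scene by ambulance clinicians". The text above the table says "Baseline data will include OHCA incidents and bystanders registered", again without a source. No row of the table, and no other section of the article, names a dispatch log, patient care record or registry extract as a source of study incidents.

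**How an incident enters the app.** The Ambulance clinician registration section says "Registration is completed via the RescQ™ app on EEAST iPad devices, which records the event with geo-location and timestamping". The QR code that lets other clinicians or bystanders register is generated by the same app. The app also "records the number of bystanders under 18 or who decline registration", so it can hold an incident with no registration, provided that a clinician opened it.

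**The concern.** This criterion exists to show whether clinicians use the pathway at the scene. An incident in which no clinician opens the app leaves no trace in the only event source listed. The Discussion expects such non-use: "Anticipated challenges include inconsistent ambulance clinician compliance given the high-pressure nature of OHCA scenes". A denominator built from that source would therefore leave out the failures that the criterion is meant to count.

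At stake is the red-amber-green result for one of the two binary progression criteria. A service with truly red uptake could be graded amber or green, and neither the exact test nor the Clopper–Pearson interval would show it, because both are conditional on the incidents that were recorded.

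**Working it through.** **1. The plan's own figure.** The inputs, from Sample size and statistical analysis, are n = 193, null 30%, alternative 40%, and a one-sided exact binomial test at α = 0.05. The smallest r with P(X ≥ r | 193, 0.30) ≤ 0.05 is r = 69 (69/193 = 35.8%). The exact α is 0.0496 and the power is P(X ≥ 69 | 193, 0.40) = 0.9001. The stated power of more than 90% is reproduced, and 193 is the smallest n that reaches it. The calculation is sound; the question is what is being counted.

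**2. Direction of the bias.** Without the app there is no registration, since the QR route also starts in the app. Every incident in which the app was never opened is therefore a zero in the numerator. Removing zeros from the denominator cannot lower a proportion.

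**3. Size, as a range.** Let u be the true uptake over all eligible incidents. Let c be the share of incidents without a registration that still leave an app record, for example because everyone declined. Then

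apparent uptake = u / (u + (1 − u) × c).

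The document gives no value for c, so c is an assumption and is varied. For u = 0.25 and c = 0.5 this is 0.25 / (0.25 + 0.75 × 0.5) = 0.25 / 0.625 = 40.0%.

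| True uptake | c = 1 | c = 0.75 | c = 0.5 | c = 0.25 |
|---|---|---|---|---|
| 20% | 20% | 25% | 33% | 50% |
| 25% | 25% | 31% | 40% | 57% |
| 30% | 30% | 36% | 46% | 63% |

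c = 1 means that every unregistered incident is captured, as an independent source would aim to do. At c = 0, when only registrations create a record, apparent uptake is 100% whatever the true rate.

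**4. Capture rate at which a low rate reads as 40%.** Setting apparent uptake to 0.40 gives c = 1.5u / (1 − u), which is 0.375 for u = 20%, 0.50 for u = 25% and 0.64 for u = 30%.

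**5. Effect on the test.** Assume 193 recorded incidents and rejection at 69 or more. An observed rate of at least 40% needs 78 of 193 (77/193 = 39.9%).

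| True uptake | c | Apparent | P(reject red zone) | Same, at c = 1 | P(observed ≥ 40%) |
|---|---|---|---|---|---|
| 20% | 0.5 | 33% | 0.26 | about 0 | 0.02 |
| 25% | 0.75 | 31% | 0.079 | 0.0006 | 0.003 |
| 25% | 0.5 | 40% | 0.900 | 0.0006 | 0.48 |
| 30% | 0.5 | 46% | 0.999 | 0.0496 | 0.95 |

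With high capture the distortion is modest. At one half or below it can change the colour.

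**The case against.** The strongest reply is that the article never says the denominator is drawn from the app. The outcome definition, Table 3 and the sample size section all speak of eligible OHCA incidents, and only the numerator mentions the app. The event row in Table 2 lists attributes of a logged event (time and place), not a count of eligible incidents. A 30/40% scale fits a denominator of all eligible incidents better than one of app-opened incidents, where uptake would usually be high. The ambulance trust is a project partner, and the full protocol, which is not shown, may name its records as the source.

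All of this stands against a stronger reading. A reader might infer that uptake is inflated as a matter of fact. The document supports only the conditional statement: it would be, if the listed source is used. Two further inferences also fail:

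- **That an eligible incident is registered almost by definition**, because Table 1 requires "Consenting bystanders". Those criteria apply to bystanders. The incident-level criterion is presumed cardiac or medical aetiology, and nothing says that an incident where everyone declined is ineligible.
- **That 193 can be set against the regional arrest caseload to show low uptake.** The 193 is the denominator needed for power, not a forecast or an observed count. A caseload for Essex would also need a national population figure that the article does not give.

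The reply does not remove the point. Leaving operational detail to an appendix would be unremarkable, but Table 2 is not silent. It assigns a source to OHCA events, and that source cannot see clinician non-use. Thresholds that suit an all-incident denominator indicate intent; they do not supply the data.

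**Conclusion.** The point holds in conditional form. On the sources that the article lists, the clinician-uptake denominator would omit incidents in which the app was never opened, and the resulting bias can only be upward. That direction needs no assumption beyond use of the listed source. The size does: c is unknown, and the figures above are illustrations. At an assumed c of 0.5, true uptake of 25% (red) reads as 40% (green), and the chance of rejecting the red zone rises from 0.0006 to 0.90.

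The power calculation is correct and is not at fault. If Appendix D already names an app-independent source, the outcome is safe and what remains is to bring Table 2 into line with it. Otherwise this primary progression criterion cannot be interpreted as it stands.

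**What to change.** The article reports the pilot as complete with analysis underway, so this should be settled before results are reported.

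1. Take eligible incidents from ambulance-service records for Essex over the 12 months.
2. Define an eligible incident as an attended OHCA of presumed cardiac or medical aetiology with at least one adult bystander, regardless of app use or consent.
3. Link app registrations to these incidents by time and location, which the app already records.
4. Report how many eligible incidents had no app record. Show uptake on the app-opened denominator only as a secondary figure.
5. Correct Table 2 so that the source of eligible incidents is named.

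The cost is one retrospective extract from a partner service plus the matching. Aetiology and bystander presence will be imperfectly coded in routine records, and the uptake figure will probably be lower.
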